#### *Radiographic assessment of OA*

The presence of radiographic OA will not be an inclusion criterion, as in clinical practice, footwear interventions are often provided on the basis of clinical findings without confirmation of radiographic changes. However, to document the radiographic severity of OA, weightbearing dorso-plantar and lateral radiographic projections will be obtained from the most symptomatic foot (or in the case of equivalent bilateral symptoms, the right foot), with the participant standing in a relaxed bipedal stance position. All x-rays will be taken by the same medical imaging department using a Shimadzu UD150LRII 50 kw/30 kHz Generator and 0.6/1.2 P18DE-80S high speed x-ray tube from a ceiling suspended tube mount. AGFA MD40 CR digital phosphor plates in a 24 cm × 30 cm cassette will be used. The tube will be angled 90 degrees and centred at the base of the third metatarsal, with the film focus distance set at 100 cm. All radiographs will be examined by [name], [name] and [name], to determine the presence of OA, using a radiographic atlas of foot OA developed by our group [55,56]. The reliability of assessments using this atlas have been reported in detail previously (kappa values greater than 0.76 [55]).

#### *Treatment preference and credibility/expectation*

In open randomised trials of musculoskeletal disorders, it has been demonstrated that participants who are allocated to their preferred treatment achieve better outcomes than those who do not receive their preferred treatment, despite the randomisation process resulting in equivalent baseline outcome measure scores [57]. To address this issue, participants will be asked if they have a preference for either treatment (documented as rocker-sole shoes, prefabricated foot orthoses or no preference), although their response will not influence their randomised group allocation [58]. This approach conserves all the advantages of a fully randomised design but enables the interaction between preference and outcomes to be quantified [59]. A related issue is treatment credibility (participants’ beliefs about the logic underpinning the intervention) and treatment expectancy (participants’ perceptions of how much they may benefit) [60]. To quantify this, the Credibility/Expectancy Questionnaire (CEQ) [61] will be administered after randomisation. The CEQ consists of six items: three related to credibility and three related to expectancy. For each item, participants will be asked to rate the credibility of the treatment and their expectations on a 9-point Likert scale. High scores on the scale indicate that the participant considers the treatment to be credible and expects the treatment to be effective. The CEQ has been shown to have good internal consistency and test-retest reliability [61], and has recently been used to assess the credibility of sham dry needling [62] and sham foot orthoses [63] used in clinical trials.

#### *Biomechanical evaluation*

Because the proposed mechanism of action of the rocker-sole shoes is a change in biomechanical function of the lower limb, two approaches will be used to evaluate their effects at the baseline appointment. First, spatio-temporal parameters and three-dimensional motion of the thigh and lower leg during gait will be recorded using a wireless, wearable sensor motion analysis system (LEGSys™, Biosensics, Boston, MA, USA). This system consists of accelerometers and gyroscopes attached with Velcro™ straps to each lower leg and thigh. The method for calculation of the spatio-temporal parameters of gait is described in detail elsewhere [64]. To summarise, the gait phases are determined from the precise events of heel-strike (initial foot contact) until toe-off (terminal foot contact). These events are extracted from gyroscopes attached to each shank through a local minimal peak detection scheme. Based on each participant’s height and using a biomechanical model, spatial parameters (i.e. stride length and stride velocity) and kinematics (knee and hip) are estimated by integration of the angular rate of rotation of the thigh and shank relative to the waist sensor. Gait analysis with this system has been validated in healthy controls [64], older people [65], and patients with hip osteoarthritis [66]. After a familiarisation period, participants will complete 4 walking trials for each footwear condition over an 8 metre distance. To exclude the effect of acceleration and deceleration steps, only the middle four steps from each trial will be included for analysis. An average recording will be determined from the 16 steps (4 steps from 4 trials) for each condition. Second, plantar pressures (specifically, peak pressure under the hallux, first MTPJ and lesser MTPJs) will be measured with the in-shoe Pedar® system (Novel GmbH, Munich, Germany), a reliable, valid and accurate measure of in-shoe pressure [67-69]. The Pedar® insoles are approximately 2 mm thick and consist of 99 capacitive pressure sensors, arranged in grid alignment. Plantar pressure data will be sampled at a frequency of 50 Hz. Both groups will undergo the same biomechanical assessment. However, for rocker-sole shoe group, comparisons will be made between their own shoes and the rocker-sole shoes, while in the prefabricated foot orthoses group, comparisons will be made when wearing their own shoes (with and without the prefabricated orthoses).

### Outcome measures

Primary and secondary outcome measures will be collected at baseline and 4, 8 and 12 weeks. These time points have been selected as 4 weeks is considered the earliest time of greatest effect and 12 weeks is considered to be a standard clinical follow-up time [17,70]. To avoid over-testing and to minimise the risk of Type I error associated with serial measurements, statistical analysis of the effectiveness of the interventions will specifically focus on the change in primary outcome measures between baseline and 12 weeks [71,72].

The primary outcome measure will be the foot pain domain of the Foot Health Status Questionnaire (FHSQ) [73]. The FHSQ is a foot-specific health-related quality of life outcome measure consisting of 13 questions that assess four domains of foot health including pain, function, footwear and general foot health. Questions within each domain are scored using a Likert response format, with an output score produced ranging from 0 to 100, with a score of 100 indicating optimum foot health and a score of 0 indicating very poor foot health. The FHSQ has been shown to have a high degree of internal consistency (Cronbach's α = 0.88) and test-retest reliability (intra-class correlation coefficient = 0.86 [73]), and has been used in several RCTs by our group [17,62,74]. A recent review recommended the use of the FHSQ in clinical trials of rheumatological foot disorders [75]. Participants treated for bilateral symptoms will be asked to describe symptoms of their most painful foot. If both feet are equally painful, the right foot will be selected as the index foot.

Secondary outcome measures will include:

(i) the function domain of the FHSQ, measured at baseline, 4, 8 and 12 weeks;

(ii) the Foot Function Index - Revised (Short Form) [76], measured at baseline and 12 weeks;

(iii) severity of pain at the first MTPJ while walking over a flat surface and during rest over the last week (each via a 100 mm visual analog scale [VAS]), measured at baseline, 4, 8 and 12 weeks;

(iv) duration and severity of stiffness at the first MTPJ after first awakening in the morning, during the last week (via a 100 mm VAS), measured at baseline, 4, 8 and 12 weeks;

(v) severity of stiffness after sitting, lying, or resting later in the day, during the last week (via a 100 mm VAS), measured at baseline, 4, 8 and 12 weeks;

(vi) global change in symptoms using a 15-point Likert scale (The responses will range from "A very great deal better" to "A very great deal worse") measured at 12 weeks;

(vii) health status (using the Short-Form-12 Version 2 questionnaire) [77], measured at baseline and 12 weeks;

(viii) use of paracetamol rescue medication (number of participants and mean consumption) and co-interventions to relieve pain at the first MTPJ, documented with a monthly diary throughout the 12 week study period;

(ix) the frequency and type of self-reported adverse events (such as falls and development of new pain in other body regions), collected at 4 weekly intervals throughout the 12 week study period;

(x) the Incidental and Planned Activity Questionnaire, a self-report questionnaire that covers the frequency and duration of several levels of planned and incidental physical activity [78], measured at baseline and 12 weeks.

To maximise response to the postal questionnaire outcome measures, we will send a postcard reminder after one week to non-responders, and then follow-up with up to three attempted contacts by telephone and/or email over a two week period.

### Sample size

The sample size for the study has been determined using an *a priori* power analysis based on the primary outcome measure: the pain domain of the FHSQ [73]. We have previously determined that the minimal important difference for this measure in people with foot pain is 13 points [79]. Using a standard deviation of 19 (derived from our recent trial [17]), a power level of 0.8, alpha level of 0.05 and accounting for a drop-out rate of 15%, a sample size of 80 participants (i.e. approximately 40 per group) will be required. We have conservatively ignored the extra precision provided by covariate analysis when estimating the sample size, and have conservatively selected a drop-out rate at the higher end of previous trials of specialised footwear and/or orthoses for lower limb OA (between 2 and 15%) [30,80-82].

### Evaluation of adherence

Adherence to the intervention in both groups will be documented at 4, 8 and 12 weeks. Participants will provide information concerning the number of hours per day and number of days they have worn their rocker-sole shoes or prefabricated foot orthoses during the previous 4 weeks. To minimise participant burden, adherence will be documented on the day with recall over the previous 4 weeks, rather than by daily diary entries.

### Complications and adverse events

Complications and adverse events associated with the intervention are unlikely. However, the questionnaires at the 4, 8 and 12 week follow-ups will provide participants with an opportunity to report any difficulties they have with the interventions, and all adverse events will be reported in the final manuscript.

### Statistical analysis

Statistical analysis will be undertaken using SPSS® version 21.0 (IBM Corp, NY, USA) using the intention-to-treat principle for all randomised participants [38]. The exception to this will be the safety outcome measures which will be analysed as treated. In participants with bilateral symptoms, the most painful foot will be analysed. Multiple imputation will be used to replace any missing data using five iterations, with age, baseline scores, and group allocation as predictors [83]. The exception will be for the variables use of rescue medication and co-interventions where no data substitution will be applied. Standard tests to assess continuous data for normal distribution will be used and transformation carried out if required. Differences in the primary and secondary outcome measures between the two groups will be compared. Continuously-scored outcome measures will be analysed using analysis of covariance with baseline scores and intervention group entered as independent variables [84]. Ordinal scaled data will be analysed using non-parametric tests. Dichotomously-scored outcome measures will be compared using relative risk, risk difference and number needed to treat. For the gait analysis component of the study, differences in biomechanical variables will be compared using paired *t*-tests and effect sizes (or in the case of non-normally distributed data, medians will be compared using Mann–Whitney U tests).

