The gait analysis component of the study will provide useful insights into the possible mechanism of action of the interventions. The wearable sensor motion analysis system (LEGSys™, Biosensics, Boston, MA, USA) provides high resolution temporal and kinematic data, without the laboratory constraints and data processing requirements of traditional motion analysis systems [89]. The use of this system will help identify changes in lower limb function associated with the footwear and orthoses (particularly changes in sagittal plane motion of the shank and thigh), and whether these changes are related to improvement in symptoms. Similarly, the in-shoe plantar pressure system (Pedar®, Novel GmbH, Munich, Germany) will identify the extent to which the high peak pressures under the hallux frequently observed in individuals with first MTPJ OA [6,90] are mitigated by the interventions. It should be noted, however, that it is not possible to measure first MTPJ motion *directly* in this study, as this requires the permanent modification of the upper of the shoe to allow placement of reflective markers or electromagnetic motion sensors on the foot.

Participants will be reviewed at 4-weekly intervals up to 12 weeks, which is similar to previous footwear trials which have employed 8 week [91] or 12 week [29,30,92] follow-up periods, and longer than the 4 week physical therapy trial for first MTPJ OA by Shamus *et al*. [16]. Although our trial of viscosupplementation for first MTPJ OA followed participants for 24 weeks, the effect of treatment clearly plateaued at 12 weeks in both groups [17]. We are therefore confident that the 12 week duration of the trial is sufficient to detect differences between the groups, if they exist. Furthermore, 12 weeks is considered to be a standard clinical follow-up period in trials evaluating the effects of interventions for OA [70]. The trial will incorporate 4 repeated measurements for the primary outcome measure (baseline, 4 weeks, 8 weeks and 12 weeks) to provide insights into the trajectory of any improvements in symptoms. However, to address the issue of multiple testing of serial measurements [71,72], we have pre-specified 12 weeks as the primary end-point, and no statistical comparisons of the 4 and 8 week scores will be undertaken.

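### The imputation model fixes age, baseline scores and group as predictors and leaves out the 4- and 8-week scores, so the week-12 comparison is unprotected if loss follows early response differently in the two arms

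*Protocol article*

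**What the plan says.** Protocol article, Statistical analysis: "Multiple imputation will be used to replace any missing data using five iterations, with age, baseline scores, and group allocation as predictors". Rescue medication and co-interventions are exempt from this rule. Continuous outcomes are compared by "analysis of covariance with baseline scores and intervention group entered as independent variables".

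Protocol article, Outcome measures: "Primary and secondary outcome measures will be collected at baseline and 4, 8 and 12 weeks". The itemised list there is narrower. FHSQ function and the pain and stiffness scales are taken at every visit. The Foot Function Index, SF-12 and activity questionnaire are taken only at baseline and week 12, and global change only at week 12.

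Protocol article, Discussion: "we have pre-specified 12 weeks as the primary end-point", and "no statistical comparisons of the 4 and 8 week scores will be undertaken". That sentence rules out between-group tests at the interim visits. It does not rule out using those scores to predict a missing week-12 value.

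Nothing in the article adds the interim scores to the imputation model or describes a sensitivity analysis for missing outcomes.

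**The concern.** This is a stated choice of model, not a detail left for a later document. Imputing an outcome from the covariates that the analysis model already uses brings in almost no new information. With age as the only addition, the result should be close to a complete-case ANCOVA plus simulation noise.

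A participant who reported little benefit at weeks 4 and 8 and then stopped replying would receive draws typical of completers of the same age, baseline score and arm. The interim answers would play no part. If such losses are commoner in one arm, that arm looks better at week 12 than it was. Participants know their allocation and report their own outcomes, so loss linked to perceived benefit is possible. The interim scores are the data that would make the missing-at-random assumption easier to defend, and they are already being collected.

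**Working it through.** **1. The plan's own figure.** The Sample size section gives a 13-point difference ("minimal important difference for this measure in people with foot pain is 13 points"), SD 19, power 0.80, alpha 0.05 (two-sided assumed) and 15% drop-out.
- n per arm = 2 × (1.960 + 0.842)² × 19² / 13² = 2 × 7.85 × 361 / 169 = 33.5, so 34.
- 34 / 0.85 = 40 per arm, 80 in total, which matches the plan.
- At 15% loss, 0.15 × 80 = 12 week-12 scores would be missing.

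**2. Simulation set-up.** There were 80 participants, SD 19, a true difference of 13 and about 15% missing at week 12. The analysis was baseline-adjusted ANCOVA pooled by Rubin's rules, with 1,500 replicates per scenario and 30 imputations. The documents give no correlations. I assume baseline to follow-up 0.5 and adjacent follow-up visits 0.7 or 0.8. All drop-outs return week 4 and about half also return week 8. *Baseline scores* is read as the baseline of the outcome being imputed.

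**3. Bias in points** (the two values are for adjacent-visit correlation 0.7 and 0.8):

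| Loss before week 12 | Complete cases | Stated predictors | Plus weeks 4 and 8 |
|---|---|---|---|
| Random | −0.06, +0.03 | −0.04, +0.04 | −0.04, +0.08 |
| Follows interim score, same in both arms | +0.11, +0.12 | +0.10, +0.11 | +0.10, +0.04 |
| Follows interim score in one arm only | +1.38, +1.96 | +1.37, +1.97 | −0.07, +0.17 |
| Opposite directions in the two arms | +2.56, +3.04 | +2.55, +3.02 | +0.05, −0.11 |

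The Monte Carlo error of each bias is about 4.1 / √1500 = 0.11, so the first two rows are compatible with zero. The stated model tracks complete cases throughout. Relative to the target, 1.4 / 13 = 11% and 3.0 / 13 = 23%.

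**4. Lower loss and other assumptions, one-arm mechanism.** Further runs of the stated model gave about 0.9, 1.4 and 2.0 points at 5%, 10% and 15% loss, and about 0 with interim scores. A run with a different selection strength, using complete-case ANCOVA as a stand-in, gave 0.4, 0.8, 1.4 and 2.2 points at 2.5%, 5%, 10% and 15%. A run with baseline to week 12 correlation 0.40, week 8 to week 12 correlation 0.75, no true effect and all loss after week 8 gave 1.8 points at about 15%.

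**5. Precision under random loss.** Adding the interim scores lowers the empirical SE from 4.12 to 4.00 (2.9%) or from 4.04 to 3.91 (3.2%). The fraction of missing information falls from 0.16 to 0.12 or 0.10.

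**6. If *iterations* means five imputed data sets.**
- Relative efficiency = 1 / (1 + 0.16 / 5) = 0.97, a loss of about 3%.
- Re-imputing the same data with new seeds moved the estimate with an SD of 0.68 points for 5 imputations and 0.22 for 50.
- With an assumed true difference of 8 points, 20 seeds gave p-values on both sides of 0.05 in 26% of data sets with 5 imputations and in 5% with 50.

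**The case against.** The stated model is valid if loss is missing at random given age, baseline and arm, and the harm needs a particular mechanism. Loss that is random, or related to response equally in both arms, leaves the comparison essentially unbiased. This stands, and it limits the point to a conditional risk.

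A reader might infer that the plan forecasts 15% loss concentrated in one arm. It does not. The Sample size section calls 15% a conservative choice at the top of a 2–15% range. The Background cites 2% over 12 weeks for the same brand of shoe in knee osteoarthritis, and the Outcome measures section provides reminders. The Discussion raises differential drop-out when explaining why both treatments are disclosed, a choice made to reduce it. Its remarks on resentful demoralisation concern adherence and questionnaire answers, not loss.

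A reader might also infer that the plan uses only five imputations. The text says *iterations*, which could mean cycles of the algorithm. In that case the number of data sets is unstated and the seed argument weakens. Nor is a drop-out given an arm average: draws depend on baseline and age and carry random variation.

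Finally, the simulations favour the remedy, because every simulated drop-out has at least one interim score. Participants who return no follow-up questionnaire gain nothing, and neither do outcomes measured only at baseline and week 12. All of this stands. None of it gives a reason to leave the interim scores out where they exist.

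**Conclusion.** The point holds as a no-cost improvement to a stated method. It does not show that the result will be biased.

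- **Bias:** conditional on loss that follows interim response and differs between arms. It is about 1 point at 5% loss and 1.4–2 points at 10–15% if this happens in one arm, and up to about 3 points at 15% if the arms run in opposite directions. Otherwise it is about 0.
- **Precision:** a gain of about 3% of the SE, which is minor.
- **Number of imputations:** an ambiguity in wording. On the five-data-set reading the seed moves the estimate by about 0.7 points SD, which matters only for a borderline result.

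These sizes rest on assumed correlations (baseline to week 12 0.4–0.5, adjacent visits 0.7–0.8), assumed selection strengths, and drop-outs having returned at least one interim questionnaire. The omission of the interim scores from the stated predictors rests on the text alone and holds on either reading of *iterations*.

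**What to change.** Reword the imputation sentence in Statistical analysis along these lines: missing week-12 outcomes will be multiply imputed, with a stated number of imputed data sets (for example 30 to 50), from group, sex, age, the baseline score and, where measured, the 4- and 8-week scores of the same outcome; results will be pooled by Rubin's rules. Missing interim scores are imputed within the same model. Sex is included because it is the stratification factor.

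Add that the interim scores serve as auxiliary predictors only, so the commitment not to test between groups at weeks 4 and 8 is unchanged. If a number of algorithm cycles is also to be given, state it separately from the number of data sets.

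The cost is one reworded sentence and a little computing time. No new data are needed and the ANCOVA is unchanged. It should be settled before outcome data are analysed.

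### The normality-test-and-transform rule covers the primary FHSQ pain score, so the data decide the scale of the primary estimate, and a transformed result could not be read against the 13-point minimal important difference

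*Protocol article*

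**What the plan says.** The Statistical analysis section sets one rule for continuous data: "Standard tests to assess continuous data for normal distribution will be used and transformation carried out if required". It then gives the model: "Continuously-scored outcome measures will be analysed using analysis of covariance with baseline scores and intervention group entered as independent variables". Between these two sentences it says that the groups will be compared on both primary and secondary outcomes. Nothing exempts the primary outcome from the rule, and model residuals are not mentioned.

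The Outcome measures section makes the FHSQ pain domain primary and describes a bounded score, "with an output score produced ranging from 0 to 100, with a score of 100 indicating optimum foot health". The Discussion fixes 12 weeks as the only time point for comparing the groups.

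The Sample size section works in the same untransformed points. It states that "the minimal important difference for this measure in people with foot pain is 13 points", takes an SD of 19 from the group's previous trial, and concludes that "a sample size of 80 participants (i.e. approximately 40 per group) will be required".

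**The concern.** Two parts of the plan pull apart. The sample size and the clinical reading of the result rest on a difference in FHSQ points. The analysis section allows the primary outcome to leave that scale, depending on how the collected data look.

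If that happens, the treatment effect becomes a ratio or a difference in transformed units. It could no longer be compared directly with 13 points, which is the comparison that tells a reader whether one intervention is better by an amount that matters. The plan restricts testing to 12 weeks to avoid multiple looks at serial measurements. Leaving the scale of that single comparison open until outcome data are seen works against the same aim.

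The rule also protects little. Analysis of covariance relies on roughly normal residuals, not on normally distributed scores, and with about 40 per arm a difference in means is not sensitive to moderate skewness.

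**Working it through.** **1. The plan's own figure.** Inputs from the Sample size section: difference 13, SD 19, power 0.80, alpha 0.05 (two-sided assumed), drop-out 15%.

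- n per arm = 2 × (1.960 + 0.842)² × 19² / 13² = 2 × 7.849 × 361 / 169 = 33.5, rounded up to 34.
- Allowing for drop-out: 34 / 0.85 = 40 per arm, 80 in total.

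The stated 80 is reproduced. The calculation is on the untransformed scale, with a standardised difference of 13 / 19 = 0.684. With 34 completers per arm, power is about 0.81 by the normal approximation and 0.79 by the t distribution.

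**2. What 13 points becomes after transformation.** The article names no transformation. Two common choices for scores that bunch near an upper limit of 100 are log(101 − y) and √(101 − y). The same 13-point gain at two starting levels:

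| Scale | 40 → 53 | 80 → 93 | Ratio |
|---|---|---|---|
| Reflected log | ln(61/48) = 0.24 | ln(21/8) = 0.97 | about 4 |
| Reflected square root | √61 − √48 = 0.88 | √21 − √8 = 1.75 | about 2 |

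The same happens with a plain log. Thirteen points is a ratio of 53/40 = 1.33 from a score of 40, but 93/80 = 1.16 from a score of 80. In the other direction, a constant ratio of 1.20 means 8 points at 40 and 16 points at 80. No single transformed value stands for the 13-point difference.

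**3. How often the rule might fire (illustration only).** The article gives the SD and the range, but no week-12 mean and no shape. Assumptions: Shapiro–Wilk at the 5% level, 34 completers per arm, normal scores with SD 19 cut off at 0 and 100, arm means 6.5 points either side of the overall mean, and 3,000 to 4,000 simulated trials per setting. Rates vary by a point or two between runs.

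| Overall mean | Rejects, pooled scores | Rejects, arm-centred residuals |
|---|---|---|
| 60 | about 5% | about 5% |
| 65 | about 12% | about 8% |
| 70 | about 39% | about 16% |
| 75 | about 80% | about 37% |

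Shape matters as much as the mean. With beta-distributed scores on 0 to 100 and the same SD, pooled scores reject 64% of the time for arm means of 60 and 73 (57% on residuals) and 99% for 75 and 75 (98% on residuals). With exactly normal, uncapped scores the rate is the nominal 5%.

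**4. Whether transformation is needed for validity.** With beta-distributed scores, SD 19, 34 per arm and no true difference, a t test on untransformed scores has a type I error of about 5% at means of 65, 75 and 80. In these settings the original scale costs nothing in error control.

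**The case against.** The strongest reply is that this is one paragraph of a journal article. The choice of test, the threshold, the transformation and any back-transformation are details that a fuller protocol or analysis plan may hold. That stands, and their absence is not the point here. What the article does state is a permission to transform that reaches the primary outcome.

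Other objections also stand in part:

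- **Raw scores.** A reader might infer that raw pooled scores will be tested. The text says only continuous data. Testing residuals would generally fire less often, as the table shows, but the scale would still depend on the data.
- **Ceiling.** A reader might infer that scores will crowd the upper limit and that the test will probably fail. The article projects no week-12 level. At a mean of 60 the capped-normal model rejects no more often than chance. If the trigger were absolute skewness above 1, fewer than 1% of the simulated trials at means of 50 to 75 would be transformed.
- **Selective choice.** A reader might infer that the scale could be picked to favour one arm. The Design section says that those conducting the analyses will be blinded, which limits this. Blinding does not make the scale fixed in advance, nor a transformed result readable in points.
- **Imputation.** A reader might infer a clash with multiple imputation, since completed data sets could disagree on the test. One scale could be chosen on the observed data and used throughout, so no weight is placed on this.
- **Reporting in points.** Nothing bars giving a difference in points beside a transformed test. Nothing requires it either.

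**Conclusion.** The concern holds in a conditional form. The scale of the primary estimate is data-dependent as written. If a transformation is triggered, the result loses its direct link to the 13-point difference on which the trial is sized, and the transformed equivalent of 13 points varies two- to fourfold between starting scores of 40 and 80 on the two reflected scales. If none is triggered, the link is intact.

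The documents do not support a claim that the sample size is wrong, that the treatment comparison would be biased, or that a transformation is likely. The illustrative trigger rates run from about 5% to nearly 100%, according to the assumed mean, shape and test. They show only that the outcome of the rule cannot be foreseen. The point is worth correcting because the remedy is simple and the rule buys the primary analysis little.

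**What to change.** Add one sentence to the Statistical analysis section. The 12-week FHSQ pain score is analysed by analysis of covariance on the original 0 to 100 scale whatever its distribution, and the baseline-adjusted mean difference is reported with a 95% confidence interval in points. Assumptions are judged on model residuals. If these are clearly violated, a robust (for example HC3) or bootstrap interval is given for the same difference. Limit transformation to unbounded, skewed secondary measures such as stiffness duration, or to sensitivity analyses.

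The sample size (34 per arm, 80 after drop-out) and data collection do not change. The small cost is that robust or bootstrap intervals may be slightly wider. HC3 and the bootstrap are two acceptable choices among several. What matters is that the estimand stays in points.
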